### Statistical analysis

Data entry and analysis will be conducted in a blinded fashion. The data collected for the groups, prior to adherence to the hygiene protocols, such as age, gender, and grade of schooling, will be compared to ascertain initial similarity. The effect of groups on primary and secondary outcomes will be assessed. When applicable (i.e OHIP-EDENT), pre-treatment values will be applied as a co-variable in the statistical model. The significance level of the tests will be 0.05. Noncompliant participants will be followed up, such as those requiring interruption of one of the hygiene protocols, and to evaluate the significance of protocol deviations. In other words, the statistical analysis will consider the participants according to the treatment received (per protocol), as well as according to the planned treatment (intention to treat (ITT)); the results will be compared.

The data will be analyzed for homogeneity; in the case of non-normal distribution, the Brunner Langer nonparametric test will be used. For the categorical variables (questionnaire) the Friedman test will be applied to compare the different time points, and the Kruskal-Wallis test will be applied to compare the groups. Correlation between the quality of life indices and the quantitative variables will be tested (Pearson correlation coefficient). The Tukey test with Bonferroni adjustment will be used for subgroup analysis. The Dunn post-test test will be used with the Kruskal-Wallis test.

A flowchart of the participants will be prepared for a detailed explanation of the characteristics of the sample and the quantification of quitters and missing participants. This part will provide the number of individuals examined, reasons for exclusion, and the number of recruited, treatment-allocated participants who complete the trial and are included in analysis at the study end. The flowchart will provide the reasons for any deviation from the protocol.

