### Planned interventions

All patients will receive verbal and written instructions according to the hygiene protocols: they should brush the palate region with a soft toothbrush and water for 2 min, once a day (Toothbrush CS 5460C Adulto Ultra Macia, Curaprox, Curaden Swiss do Brasil Imp. Exp. LTDA, São Caetano do Sul, São Paulo, Brasil); immerse their dentures in the specific product once a day for the length of time proposed by the manufacturer; and brush the prosthesis for 2 min using a specific brush (Prosthesis Brush BDC150/152/153, Curaprox, Curaden Swiss do Brasil Imp. Exp. LTDA, São Caetano do Sul, São Paulo, Brazil) and neutral soap, three times a day. In addition, all patients will be instructed to remove the prosthesis during the night and leave it in a container with clean water, and in the morning to rinse the prosthesis under running water before inserting it into the oral cavity. Neutral soap and the solutions will be available to participants in identical dosing vials and in sufficient quantity for continuous use for 10 days; for greater control and monitoring of the hygiene protocol. citric acid in the form of an effervescent tablet will be removed from the package and placed in neutral packaging.

The parallel groups as determined by the different hygiene protocols will each consist of 25 participants. The protocols are as follows:
Group 1 (G1 (control group)) - brushing the palate with a soft brush and prosthesis immersion in 0.25% sodium hypochlorite solution (control group)Group 2 (G2) - brushing the palate with a soft brush and prosthesis immersion in 0.15% triclosan solutionGroup 3 (G3) - brushing the palate with a soft brush and prosthesis immersion in citric acid (Nitradine, Bonyf AG, Liechtenstein, Switzerland)Group 4 (G4) - prosthesis immersion and brushing of the palate with citric acid and a soft brush (Nitradine, Bonyf AG, Liechtenstein, Switzerland)

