### Randomization, allocation, and blinding

The study will be double-blind, and to achieve this, each researcher (R) will have an assignment during the experiment: participants will be distributed into groups taking into account a random numerical sequence (on a 1:1:1:1 ratio) generated by a computer; a researcher (R1) who is not involved in the clinical steps will place the patients’ identification numbers in an envelope, using a blinded approach, and also will prepare the products. Another researcher (R2) will be responsible for opening the envelope at the moment of the delivery of the appropriate product to the patients, according to the hygiene protocols, and examine the patients and collect samples. A third researcher (R3) will distribute the protocols and orientate the participant, and finally the researcher R4 will perform blinded statistical analysis of the data. The researchers involved in the clinical steps (R2 and R3) and the patients will not be blinded because of the nature of the intervention. Patients’ allocated interventions will not be revealed until the statistical analysis is completed.

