### Sample size estimation

Sample size for the quantitative outcomes was determined based on the primary outcome of this study (denture-related stomatitis remission). According to a previous trial [11], we used standard deviation of 2.19 (group 1 - saline group) and 1.79 (group 2 - sodium hypochlorite), a 95% confidence interval (bilateral), and a detectable difference of at least 2 logs. Based on power of 80%, this clinical study requires at least 21 participants. An additional 20% will be added to the planned sample to compensate for possible dropouts, thus resulting in a total of 25 participants.

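### Comparing the arms at baseline cannot establish that they are similar with 25 per arm, and baseline adjustment of the primary stomatitis score is not fixed (minor)

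*Protocol article*

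**What the plan says.** All of this is in the protocol article.

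- **Statistical analysis, baseline comparison:** pre-intervention data, "such as age, gender, and grade of schooling, will be compared to ascertain initial similarity". No test or margin is named, and no consequence is attached to finding a difference or finding none.
- **Statistical analysis, alpha:** "The significance level of the tests will be 0.05". This is a general statement and is not tied to the baseline comparison.
- **Statistical analysis, adjustment:** "When applicable (i.e OHIP-EDENT), pre-treatment values will be applied as a co-variable in the statistical model". Which outcomes count as applicable is not defined beyond the one named.
- **Planned interventions:** "The parallel groups as determined by the different hygiene protocols will each consist of 25 participants".
- **Randomization, allocation, and blinding:** a "random numerical sequence (on a 1:1:1:1 ratio) generated by a computer". No stratification is mentioned.
- **Study outcomes and Eligibility criteria:** the primary outcome, a stomatitis score read from photographs, is taken at baseline and at 10 days. Entry covers stomatitis types IB, II and III, so baseline severity varies between participants.

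**The concern.** The baseline sentence states a purpose: the comparison is meant to establish that the arms start out alike. A significance test cannot do that. It has no margin within which arms would count as alike, and with 25 per arm it has little ability to flag a moderate gap. A significant result is no more useful, because under proper randomisation the null hypothesis is true by design.

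Whether an imbalance matters depends on its size and on how strongly the variable predicts the outcome, not on its p-value. The protection is covariate adjustment fixed in advance. Here that is named for one secondary score only. At stake are the precision of the arm comparisons, their accuracy in a trial that happens to be unbalanced on a prognostic variable, and a published statement of similarity that the data would not support.

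**Working it through.** The plan gives no figure for the baseline comparison, so there is none to reproduce.

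**Inputs from the article:** four arms, 25 per arm, alpha 0.05 (two-sided, as in Sample size estimation). How the 25 was derived does not enter.

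**Assumptions:** the baseline comparison is a test at 0.05. The variable is roughly normal, as age might be. Gender and schooling are categorical and the simulation below does not cover them.

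**1. How large an observed gap can be without reaching p<0.05**

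- Two-arm t-test: t(0.975; 48) × √(2/25) = 2.011 × 0.283 = 0.57 SD.
- Four-arm F test: the critical F(3, 96) is 2.70, so the squared deviations of the arm means may sum to 3 × 2.70 / 25 = 0.324. The largest pairwise gap is then:
  - two arms against two: √0.324 = 0.57 SD
  - one arm against three: √(0.324 / 0.75) = 0.66 SD
  - two extreme arms with the others midway: 2 × √(0.324 / 2) = 0.80 SD

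**2. How often chance gaps arise and go unflagged**

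Each arm mean has standard error 1/√25 = 0.2 SD. From 200,000 simulated randomisations into four arms:

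| Largest gap between any two arms | Share of baseline variables | Of these, F test non-significant |
|---|---|---|
| ≥ 0.5 SD | 29% | 83% |
| ≥ 0.6 SD | 15% | 66% |
| ≥ 0.7 SD | 6% | 35% |
| ≥ 0.8 SD | 2% | 7% |

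**3. False alarms**

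With three independent variables tested at 0.05, at least one is significant by chance in 1 − 0.95³ = 14% of trials.

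**4. Effect of an unadjusted 0.5 SD imbalance**

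The article gives no baseline-outcome correlation ρ, so 0.3, 0.5 and 0.7 are assumed. For two arms compared on follow-up values alone, the shift is ρ × 0.5 SD. For the type I error conditional on that imbalance, the test statistic has mean ρ × 0.5 / √(2/25) and SD √(1 − ρ²). Adjustment multiplies residual variance by 1 − ρ².

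| Assumed ρ | Shift | Conditional type I error | Residual variance factor if adjusted |
|---|---|---|---|
| 0.3 | 0.15 SD | 0.07 | 0.91 |
| 0.5 | 0.25 SD | 0.11 | 0.75 |
| 0.7 | 0.35 SD | 0.16 | 0.51 |

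Averaged over all randomisations, the type I error remains 0.05.

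**The case against.** A reader might infer that the plan will declare most sizeable imbalances similar at 0.05 and then leave them uncorrected. The article does not support that, for four reasons.

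- **The test is inferred.** The text says only that the data will be compared, and the 0.05 sentence comes later and is general. A descriptive comparison would fit the words.
- **No decision hangs on the result.** Nothing says that adjustment is dropped if the arms look alike. Covariate use depends on applicability, not on a similarity verdict.
- **Baseline values are not ignored.** Besides the covariate sentence, the plan has analyses across time points (Brunner-Langer, and Friedman for questionnaires), and the systemic measures treat each patient as their own control.
- **Size matters.** Most gaps of 0.7 SD or more are flagged. Power against a true 0.5 SD difference (0.41 for a two-arm t-test) is also beside the point, because the true difference under randomisation is zero.

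It can be added that this is a condensed article and that a full analysis plan may list covariates.

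These objections remove the stronger reading but leave two things standing. The stated purpose of establishing similarity is in the text, and a p-value cannot serve it. And the adjustment rule as written is open for the primary outcome. Before-after analysis does not close that gap: with equal SDs at both visits, a change score carries a shift of (1 − ρ) × 0.5 SD in the opposite direction, that is 0.35, 0.25 or 0.15 SD for ρ of 0.3, 0.5 or 0.7. Friedman and Kruskal-Wallis tests, assigned to the questionnaire variables, take no covariate at all.

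**Conclusion.** The point holds in limited form, and its severity is minor. If the baseline comparison is a test at 0.05, a non-significant result with 25 per arm is not evidence of similarity: about 29% of baseline variables will show a gap of at least 0.5 SD between some two arms, and about 83% of those will be non-significant. Separately, adjustment of the primary stomatitis score, and of other outcomes measured at baseline, is not assured by the wording.

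The overall type I error is not inflated. The cost is lost precision, a conditional shift of 0.15 to 0.35 SD for an unadjusted 0.5 SD imbalance over the assumed correlations of 0.3 to 0.7, and a similarity statement without support. The conditional shift arises only for variables that predict the outcome.

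**What to change.** 1. Replace the similarity comparison with a descriptive baseline table by arm, and draw no conclusion about similarity from p>0.05.
2. State that the primary stomatitis score, and each other outcome measured at baseline, is adjusted for its own baseline value whatever the observed balance. Use a model that takes a covariate, for example an ordinal or rank-based model for scores.
3. If age, gender or schooling is thought prognostic, name it as a covariate in advance. Adjusting for an outcome's own baseline value does not correct an imbalance in these variables.

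The change affects analysis wording only. The baseline values are already collected, and each own-baseline term costs about one degree of freedom. Because the Trial status section reports that clinical results are already being analysed, the rule should be dated and its timing relative to unblinding reported.

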**Material/design:**

A clinical trial, randomized, double-blind, and with parallel groups, will be conducted in Brazil The sample will consist of 100 patients without teeth in both arches, users of at least maxillary complete dentures, and diagnosed with DS, who will be allocated to groups (*n* = 25 per group) according to the different hygiene protocols: (1) brushing of the palate and immersion of the prosthesis in 0.25% sodium hypochlorite solution (positive control); (2) brushing of the palate and immersion of the prosthesis in 0.15% triclosan solution; (3) brushing of the palate and immersion of the prosthesis in lactose monohydrate; or (4) brushing the palate with citric acid and immersing the prosthesis in lactose monohydrate. The response variables will be heart rate variability and alteration of blood pressure (systemic level), remission of DS, removal of biofilm, reduction of microbial load (colony-forming units (CFU)), mouth and prosthesis odor level, expression of MUC1, proinflammatory cytokines, C-reactive protein (CRP), viscosity, pH and salivary flow (locally); patient-centred qualitative analysis will also be undertaken. Measurements will be performed at baseline and 10 days after the interventions. The results obtained will be statistically analyzed as pertinent, with a level of significance of 0.05.

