### Study hypothesis

The primary null hypothesis of the trial is that there is no difference between the protocols for the prevention and treatment of local and systemic inflammatory responses and cardiovascular risk.

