### Study outcomes

#### Primary: denture-related stomatitis remission

To evaluate the effect of the hygiene protocols on DS remission, the participants will be examined under the baseline condition and also 10 days after starting their specific use of the protocol. To quantify the inflammation, standardized photographs of the palate will be obtained (Digital Camera, Canon EOS, Canon EF 100 mm/2: 8 Macro Lens and Canon ML3 Circular Flash), with the focus centered on the median raphe region. The images will be transferred to the computer and two blinded, previously trained researchers will assign scores according to the classification of Kabawat et al. [10].

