#### Secondary

##### Systemic evaluation

Patients’ blood pressure will be indirectly measured by the oscillatory sphygmomanometer method using an automated device (HEM7130, Omron Healthcare Brazil, São Paulo, SP); two to three measurements will be performed with a 5-min interval, recording the systolic (maximum) and diastolic (minimum) blood pressure. The technique for obtaining and classifying the individuals will follow the categorization proposed by the American Heart Association (2019).

Patients will be referred for continuous electrocardiographic monitoring with the Einthoven’s II lead, combined with monitoring of the respiratory rate with an elastic strap holding a stretch sensor around the thorax. The electrocardiogram and the respiratory sensor signal will be filtered (100 Hz to 0.5 kHz), amplified (BioAmp ADInstruments, Bella Vista Australia), digitalized (PowerLab 2/20 ADInstruments Bella Vista, Australia) and sampled (1000 Hz) continuously, using an IBM/PC. The files with the electrocardiogram recordings will be processed using a computer program (ECG Module for LabChart, ADInstruments, Bella Vista, Australia), which identifies the QRS complex of the electrocardiogram and calculates the duration of successive intervals between R waves (RR interval or cardiac interval). This processing will allow the generation of time series, beat-to-beat, from the cardiac interval values.

Cardiac interval variability will be analyzed using these recordings (spectral analysis). The series with RR interval values will be re-sampled at 3 Hz by cubic interpolation, to regularize the interval between beats. The series with interpolated RR interval values will be divided into segments with 512 values each, with a 50% overlap. The stationarity of each segment will be examined visually, and those with artifacts or transients will be excluded. Each segment will have its spectrum calculated by fast Fourier transform (FFT) after hanning windowing. The RR range spectra will be integrated into low frequency (LF) (0.04–0.15 Hz) and high frequency (HF) (0.15–0.50 Hz) bands. The relative power (normalized units) of the RR interval spectra in each frequency band, and the ratio of the LF and HF (LF/HF) powers thereof, will be determined.

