## Discussion

This RCT will provide a guideline for clinical practice on the use of hygiene protocols in the treatment of oral diseases mediated by biofilm (DS). Also, it may provide evidence of correlation between oral manifestation and cardiac risk.

DS has been recently associated with systemic implications (variations in blood pressure and endothelial dysfunction) that precede the development of serious cardiovascular disorders, such as atherosclerosis and hypertension, which are changes in general health with high mortality/morbidity rates [16–18]. However, the mechanisms that are related to correlation between oral inflammation and cardiovascular effects are not yet fully described; one of the most important hypotheses is the pre-activation of the immune system [17].

The information from this study will also improve clinical decision-making and potentially protect edentate patients from harm caused by ineffective treatment, and the incorporation of hygiene protocols for oral tissues and prostheses can achieve favorable results associated with low costs and minimal adverse effects, besides possibly avoiding the involvement of opportunistic diseases, which may lead to a decreased risk of cardiac diseases. The resulting published information will provide evidence for the development of clinical recommendations for DS, which will not only be used for publication in indexed journals but also for public health information services.

Thus, we predict a favorable impact on public health, while the results will provide the basis for future investigations of the characterization of possible changes in HRV, correlated or not, with changes in blood pressure, salivary proinflammatory markers and salivary parameters with DS. Given the vast prevalence of DS in this elderly population, such knowledge may be crucial for effective control as well as for the detection of cardiovascular disease risk.

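### One flat 0.05 level covers the primary and about 25 secondary outcomes, while the primary null hypothesis is worded widely enough to take in the secondary markers

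*Protocol article*

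**What the plan says.** The outcomes section separates one primary outcome, headed "Primary: denture-related stomatitis remission", from a long secondary list covering systemic and local parameters. The Study hypothesis section is wider. Its primary null hypothesis is that the protocols do not differ "for the prevention and treatment of local and systemic inflammatory responses and cardiovascular risk".

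The Statistical analysis section treats both tiers together: "The effect of groups on primary and secondary outcomes will be assessed", followed by "The significance level of the tests will be 0.05". It provides Tukey with Bonferroni, and Dunn after Kruskal-Wallis. These handle comparisons among groups inside one endpoint, not across endpoints. No secondary outcome is ranked or labelled exploratory.

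The abstract gives one undivided list, with the systemic measures first and DS remission not marked as primary: "The response variables will be heart rate variability and alteration of blood pressure (systemic level), remission of DS, removal of biofilm". The Discussion says the trial will provide a guideline for clinical practice, and adds: "Also, it may provide evidence of correlation between oral manifestation and cardiac risk".

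**The concern.** The outcome named as primary and the hypothesis named as primary do not match. DS remission is one outcome and can be tested at 0.05. The hypothesis as worded also covers systemic inflammation and cardiovascular risk, which only the secondary measures can address. Read with a flat 0.05 for every test, a significant difference in, say, one salivary cytokine or one heart rate variability index could be reported as a rejection of the primary null hypothesis.

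What is at stake is which conclusions count as confirmed. The cardiovascular part is the most open to this, because no single blood pressure or heart rate variability measure is designated to carry it.

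**Working it through.** **1. The plan's own figure.** The document states no family-wise error rate. Its only figure is the per-test level of 0.05, so there is nothing to reproduce, and the check asks what that level implies.

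**2. Count of secondary tests** (from Systemic evaluation and Local parameters):

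- Systemic: systolic and diastolic pressure ("recording the systolic (maximum) and diastolic (minimum) blood pressure") 2; normalized LF and HF power counted once 1; LF/HF ratio 1; 0V and 2V 2; SampEn 1. Sum 2 + 1 + 1 + 2 + 1 = 7.
- Local: biofilm area 1; CFU for 4 culture groups at 2 sites 8; mouth and prosthesis odor 2; MUC1 1; IL-6 and TNF-α 2; CRP 1; viscosity, pH and flow 3. Sum 1 + 8 + 2 + 1 + 2 + 1 + 3 = 18.
- Total 7 + 18 = 25, or 26 if LF and HF are counted separately. OHIP-EDENT domains and VAS items at days 10 and 30 are left out, as are post-hoc pairs.

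**3. Independent endpoints, all nulls true.** P(at least one p < 0.05) = 1 − 0.95^m.

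- m = 7: 1 − 0.95^7 = 0.302
- m = 25: 1 − 0.95^25 = 0.723
- m = 26: 1 − 0.95^26 = 0.736

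The expected number of false positives for m = 25 is 25 × 0.05 = 1.25, whatever the correlation.

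**4. Correlated endpoints.** Simulation with four arms ("on a 1:1:1:1 ratio") of 25 each, normal endpoints with a common correlation, one 3-df F test per endpoint at 0.05, and 4,000 trials per cell. The correlations are assumptions.

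| Assumed correlation | 7 systemic | 25 secondary |
|---|---|---|
| 0 | 0.304 | 0.727 |
| 0.3 | 0.269 | 0.623 |
| 0.5 | 0.248 | 0.497 |
| 0.8 | 0.150 | 0.254 |

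A separate simulation of the 25-endpoint case gave 0.718, 0.610, 0.493 and 0.255 at the same correlations.

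**5. A different correlation structure.** With 26 endpoints correlated mainly within families, the rate was 0.677 (within 0.5, between 0), 0.592 (within 0.7, between 0.2) and 0.481 (within 0.9, between 0.1). These all lie inside the range in step 4.

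**6. Against the stated level.** For 25 endpoints, 0.25/0.05 = 5 and 0.73/0.05 ≈ 15. For the 7 systemic endpoints, 0.15/0.05 = 3 and 0.30/0.05 = 6.

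**The case against.** A single primary outcome with unadjusted secondary outcomes is common, and the handling of secondary multiplicity is often left to an analysis plan that is not shown here. That stands: the absence of a secondary testing strategy would not be a finding by itself. What remains is what the article does state, namely a flat 0.05 for both tiers and a primary hypothesis wider than the primary outcome. An unseen analysis plan would leave that published hypothesis as it is.

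Four stronger readings are tempting, and the document does not support them.

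- *There is no hierarchy at all.* The outcomes section separates one primary outcome, and the sample size section is based on it. Ranking is absent only among the secondary outcomes.
- *A false positive is about as likely as not.* That figure needs a common correlation near 0.5 and equality of all protocols on every endpoint. The document gives no correlations, so only the range can be stated.
- *Clinical and cardiac claims are announced from the secondary outcomes.* The guideline sentence covers the trial as a whole, including DS remission. The cardiac sentence is conditional and concerns correlation, and the Discussion also presents heart rate variability changes as a basis for future work.
- *The 7-endpoint figure is the error rate of the cardiac claim.* It describes between-arm tests. The cardiac sentence concerns correlation, and the systemic section also describes before-and-after comparison within each patient. The figure applies only to the group effects that the Statistical analysis section says will be assessed.

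**Conclusion.** The point holds as an inconsistency between the primary hypothesis, the primary outcome and the testing rule. Followed as written, about 25 secondary tests bear on the hypothesis called primary, each at 0.05, and nothing controls error across them. If the protocols do not differ on any endpoint, the chance of at least one significant secondary omnibus test is about 25% to 73% for 25 endpoints, and about 15% to 30% for the 7 systemic ones.

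These figures assume a common correlation between 0.8 and 0, approximately normal endpoints, one omnibus test per endpoint, and a count that is a reading of the measurement sections. They do not touch the test of DS remission itself. The change is worth making because it settles what the trial may claim as confirmed.

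**What to change.** - **Study hypothesis:** restrict the primary null hypothesis to DS remission at day 10.
- **Statistical analysis:** state that DS remission at day 10 is the only confirmatory outcome at 0.05. Label the other outcomes exploratory and report them as estimates with 95% intervals.
- **Abstract:** mark DS remission as primary in the list of response variables.
- **Discussion (abstract and main text):** describe any cardiovascular result as hypothesis-generating.
- **If a confirmatory secondary claim is wanted:** use a short ordered list tested only after a significant primary result, and only for outcomes not yet seen by group. Trial status says clinical results are already being analysed while cytokine and MUC1 analyses have yet to start. Those laboratory outcomes could qualify; an order chosen now among clinical measures already analysed would not be credible.

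The cost is wording only, with no new data or patients. The downside is that secondary results can no longer be claimed as confirmed.

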Symbolic analysis searches for patterns of changes between successive cardiac interval values, classifies these changes and quantifies their occurrence. Sequences of three symbols will then be analyzed and classified into four different families, according to the number of variations found. The frequency of occurrence of each pattern will be analyzed and indicated as 0 V%, 1 V%, and 2 V%. The frequency of variations of type 0 V (sympathetic) and 2 V (vagal) are of interest as indicators of cardiocirculatory autonomic modulation.

The sampling entropy (SampEn) will be calculated from the IC series with the help of the JBioS software. The number of practical terms, SampEn quantifies the (logarithmic) probability that near-size patterns *m* will continue to *m* + 1. In other words, of the size patterns *m* that are similar, SampEn indicates which percentage of these will remain similar for *m* + 1, that is, when an extra point is considered. High probability of the patterns continuing closely indicates regularity, yielding low values of entropy. Cardiac variability and blood pressure will be recorded in the control period and after the treatment of DS through hygiene protocols. Thus, each patient will be their own control.

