##### Local parameters

To verify biofilm removal on the inner surface of the upper prosthesis, the technique described will be performed according to Badaró et al. [11], such that from the biofilm evidence, the prostheses will be photographed in standardized positions. The areas of biofilm and the surface of the prosthesis will be calculated using software and will be applied in a formula to identify the amount of total area of the biofilm, before and after treatment.

The microbial load of the prostheses and the palate will be evaluated. Biofilm at these sites will be collected according to the protocol recommended by Kabawat et al. [10] and de Souza et al. [29]. Serial dilutions will then be obtained, which will be seeded in Petri dishes with culture medium specific for the growth of *Staphylococcus* spp. (Mannitol Salt Agar, Kasvi Imp. e Dist. de Prod. para Laboratórios Ltda, Curitiba, Brazil), Gram-negative bacteria (MacConkey Agar, Himedia Laboratórios PVI Ltd., Mumbai, India), *Candida* spp. (CHROMagar™ *Candida*, Becton Dickinson, Paris, France) and *Streptococcus mutans* (SB20 Modified Agar with Casitone, Himedia Laboratories PVI Ltd., Mumbai, India)*,* and incubated in a microbiological stove (De Leo Equipamentos Laboratoriais, Porto Alegre, RS, Brazil) at 37 °C for 48 h. *S*. *mutans* will be anaerobically cultivated in a microaerophilic environment in a jar (Permution, Curitiba, PR, Brazil). After the incubation period, the CFU count will be performed to quantify the microbial load. The biological specimens present in the collected biofilm will be stored at − 80 °C for future analysis, if utilized; we will formally communicate any amendments to the protocol during the trial.

The Breath Alert™ portable device (Tanita Corporation®-Japan), used according to the manufacturer’s instructions, will measure the odor of the cavity with and without the dentures. The odor level will be given as a score determined using the apparatus, with values that can vary from 1 to 4. Thus, the odor is classified according to the scores [30] as (1) odorless, normal; (2) mild, normal odor; (3) moderate, bad breath - perceptible; or (4) strong odor, noticeable. The patient will be evaluated for odor without the prosthesis in position and then with the prosthesis seated in the oral cavity. Thus, the odor related to the prosthesis will be calculated based on the difference between the odor of the cavity with and without the prosthesis.

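### Baseline adjustment is named only for OHIP-EDENT, so the quantitative secondary outcomes either go without it or are left to the analyst's choice

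*Protocol article*

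**What the plan says.** The only covariate rule in the protocol article is in Statistical analysis: "When applicable (i.e OHIP-EDENT), pre-treatment values will be applied as a co-variable in the statistical model". OHIP-EDENT is the only outcome it names, and no other section names a baseline covariate.

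Baseline values are planned well beyond OHIP-EDENT:

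- The abstract says of the response variables in general: "Measurements will be performed at baseline and 10 days after the interventions".
- Systemic evaluation says: "Cardiac variability and blood pressure will be recorded in the control period and after the treatment of DS through hygiene protocols", and adds: "Thus, each patient will be their own control".
- Local parameters has the biofilm formula "identify the amount of total area of the biofilm, before and after treatment".
- For colony counts and salivary measures, the baseline rests on the general statement in the abstract.

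On methods, Statistical analysis says that "in the case of non-normal distribution, the Brunner Langer nonparametric test will be used". Questionnaire variables go to rank tests: "For the categorical variables (questionnaire) the Friedman test will be applied to compare the different time points". No model is named for quantitative outcomes that are normally distributed. On the error rate: "The significance level of the tests will be 0.05".

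**The concern.** The quantitative secondary outcomes carry the inflammatory and cardiovascular parts of the null hypothesis, with 25 participants per arm before dropout. In a group of that size the participant's own baseline is usually the most useful covariate available, and here it is collected anyway. Used as a covariate, it reduces the residual variance and corrects the estimate for chance differences between arms at baseline.

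The rule does not secure this. On the literal reading the covariate is limited to one questionnaire. On the loose reading the phrase about applicability carries no criterion, so whether systolic pressure or biofilm area is adjusted can be settled after the data are seen.

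The point is limited to the quantitative secondary outcomes. It does not cover the ordinal stomatitis score, or the fit between OHIP-EDENT adjustment and the rank tests listed for questionnaires.

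**Working it through.** **Inputs from the article.** Two visits, baseline and day 10; level 0.05; 25 per arm, which leaves 20 if 20% drop out (25 × 0.8 = 20).

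**Assumed inputs.** The article gives no correlation r between baseline and day 10, so r = 0.3, 0.5 and 0.7 are used. The variance is taken as equal at both visits. For power, the true difference is taken as 0.8 of the day-10 SD, with a two-sided test. There is no figure in the plan to reproduce on this point.

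**Variance of the between-arm difference, relative to a day-10-only comparison**

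- Day 10 only: 1.
- Change from baseline: 2(1 − r). With two visits and a linear model, the arm-by-time test is this same comparison.
- Day 10 adjusted for baseline: 1 − r², for large samples.
- Adjusted over change: (1 − r²) / [2(1 − r)] = (1 + r)/2.

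| r | Change | Adjusted | Adjusted ÷ change | Adjusted ÷ day 10 only |
|---|---|---|---|---|
| 0.3 | 1.40 | 0.91 | 0.65 | 0.91 |
| 0.5 | 1.00 | 0.75 | 0.75 | 0.75 |
| 0.7 | 0.60 | 0.51 | 0.85 | 0.51 |

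Below r = 0.5, change from baseline is less precise than ignoring the baseline altogether.

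**Cost of estimating the slope.** In a two-arm comparison with n per arm, the adjusted variance is multiplied on average by 1 + 1/(2n − 4). At n = 20 this is 1 + 1/36, or about 3%. The ratios to change become 0.67, 0.77 and 0.87; those to day 10 only become 0.94, 0.77 and 0.52. Adjustment loses to day 10 only when (1 − r²)(37/36) exceeds 1, that is when r² < 1/37, or r below about 0.16.

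**Power, two-sample t test, 0.8 SD difference, two-sided 0.05**

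| Per arm | r | Day 10 only | Change | Adjusted |
|---|---|---|---|---|
| 20 | 0.3 | 69% | 55% | 73% |
| 20 | 0.5 | 69% | 69% | 81% |
| 20 | 0.7 | 69% | 89% | 93% |
| 25 | 0.3 | 79% | 65% | 83% |
| 25 | 0.5 | 79% | 79% | 89% |
| 25 | 0.7 | 79% | 95% | 97% |

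The adjusted column uses 1 − r² without the slope cost. With that cost and the lost degree of freedom, the values at 20 per arm are 72%, 80% and 93%.

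**Which comparator applies.** The own-control sentence covers HRV and blood pressure only, and fits the change column. Brunner-Langer takes baseline as one of the repeated time points, so it resembles the arm-by-time case, though linear variance factors do not carry over exactly to ranks. The day-10-only column shows what would follow if that analysis were chosen; the article does not name it.

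**The case against.** The strongest case against is that the article does not fix a wrong analysis. The rule opens with a general condition. The abbreviation after it may have been meant as *for example*, in an article whose English is loose elsewhere. A reader might infer that these outcomes are definitely excluded from adjustment and will be compared with avoidable variance. The text does not support that: no sentence says that other outcomes will go unadjusted, and no model is named for normally distributed data. Nor does it support the inference that baseline is ignored. Brunner-Langer uses it as a time point, and the own-control sentence uses it for HRV and blood pressure. That sentence cannot be stretched to colony counts, biofilm or saliva.

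The sizes are also conditional. They depend on an assumed r and on equal variances, which is doubtful for counts and biofilm that treatment is meant to change. The gain over day 10 only is small at r = 0.3, about four power points. Randomisation already makes all three comparisons unbiased; adjustment deals with chance imbalance in the sample at hand.

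It can also be said that per-outcome models belong in an analysis plan that is not shown. That does not dispose of the point. The article does state a covariate rule, and the rule is either too narrow or open-ended. An analysis plan that adjusted every outcome would contradict its literal wording.

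**Conclusion.** The point holds as a defect in how the baseline rule is fixed, not as proof that the outcomes will be analysed inefficiently. The article names one outcome for adjustment and gives no criterion for the rest, while planning a baseline for all of them.

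The cost is in precision: 15% to 35% of the variance against a change or arm-by-time analysis, and 9% to 49% against day 10 only if that were used, less about 3% for the slope at 20 per arm. These figures rest on r between 0.3 and 0.7 and on equal variances. Outside those assumptions the size changes, but for a linear analysis adjustment stays at least as precise in large samples. The validity of the randomised comparison is not in question. A change is worth making because it needs no new data and removes an analyst's choice.

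**What to change.** Replace the covariate sentence, as it applies to the quantitative secondary outcomes, with:

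> For each quantitative secondary outcome measured at baseline, the day-10 value will be compared between arms in a linear model with arm and the participant's own baseline value (log10(CFU+1) for counts, log scale for skewed salivary markers and LF/HF). Where residuals remain clearly non-normal, a rank-based analysis adjusted for baseline, or the stated Brunner-Langer analysis, will be used.

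Adding 1 to the count handles zero counts, and the second sentence keeps the nonparametric fallback.

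Trial status says that clinical results are already being analysed, with cytokine and MUC1 analyses still to start. Randomization, allocation, and blinding says that allocations stay unrevealed until the statistical analysis is complete. Record the change with its date before allocation is revealed. For any outcome already analysed unblinded, label the adjusted analysis as added later.

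The cost is one degree of freedom per model, a negligible loss of precision if r is below about 0.16, and a short amendment. No extra data are needed.
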